## Abstract

School-based programmes need to be effective, easy for all, easy to perform within a short duration, and inexpensive. However, no studies have reported whether voluntarily and very short-time active play programmes contribute to improved health outcomes. This study aims to describe the GRoup activity, Active Play and Exercise (GRAPE) cluster randomised controlled trial that examined whether active play interventions of very short durations contribute to increasing physical activity (PA) and bone mass among school-aged children. The trial was conducted in 2018 from January to June, and the activity comprised ≥2 children jumping together for approximately 10 s per session, at least five times a day (approximately 1 min/day). School clusters, pair-matched as per school size (total number of children) and region, were randomly allocated to either intervention or wait-list control groups. The primary outcomes comprised objectively measured changes in PA levels (moderate-to-vigorous PA) evaluated using wrist-worn activity trackers from baseline to the one-year follow-up (six-month post-intervention follow-up) and changes in bone mass evaluated using calcaneus quantitative ultrasound parameters. This study could describe the problems and challenges in school-based PA intervention studies and present findings that could make a potentially important contribution to health education and PA promotion.

## 1. Introduction

Physical activity (PA) is associated with numerous health benefits across an individual’s lifespan [1,2]. Particularly, PA in childhood is one of the most effective preventive strategies to fight osteoporosis later in life [3]. Evidence also indicates that PA is associated with better mental health among children and adolescents [4]. In addition to improving physical and mental health, PA in childhood also promotes certain aspects of social health, such as non-cognitive skills [5] and labour market outcomes in later life [6,7]. Despite these benefits, globally, 81% of children and adolescents aged 11–17 years do not meet the recommended guideline of at least 60 min of moderate-to-vigorous PA (MVPA) daily [8,9].

Among Japanese children, 51.4% of the boys and 70.0% of the girls in fifth grade (aged 10–11 years) engage in exercise for less than 420 min/week, excluding physical education classes [10]. Additionally, owing to the prominent segregation of the time spent in PA or sports participation [11], there is a concern that children who are not good at and/or dislike exercise may have fewer opportunities to participate in exercise or sports. Therefore, the Japan Sports Agency (JSA) and the Ministry of Education, Culture, Sport, Science and Technology-Japan (MEXT) conduct yearly national surveys of physical fitness and lifestyle habits, including PA, and support initiatives derived from the detailed analyses of these surveys to improve physical fitness in Japan. Moreover, the JSA and MEXT spread awareness of the importance of physical fitness among children, providing them with opportunities to familiarise with exercise and sports, and nurture qualities and abilities needed to enjoy sports throughout their lives [12,13].

Present evidence suggests that school-based exercise programmes improve various health indicators among children [14,15,16,17,18]. However, implementing additional programmes may not be feasible in Japanese schools since the regular curriculum is on a tight schedule, requiring several additional tasks to be performed [19]. Furthermore, most evaluations of any feasible, implemented, school-based PA promotion programmes comprised one-arm comparisons (before and after) wherein the effects relative to the control group were insufficiently explored [10]. Therefore, school-based programmes need to be effective, easy for all, easy to perform within a short duration, and inexpensive. The “Bounce at the Bell” programme can be easily implemented by elementary school teachers within a few minutes (~3 min) each day, enhancing bone mass in children [20]. However, there is no evidence of the effect of exercising for less than 3 min a day on a child’s bone mass and other health factors. Moreover, there is strong evidence that supervised exercise, such as physical education, is one of the effective ways to increase PA [21]. However, it is difficult for participants to develop an exercise habit and keep it up when the intervention stops; therefore, long-term effects of interventions are questionable [18]. Health education at school, therefore, requires designing of educational methods and strategies (intervention) so that children can voluntarily (or self-determined) rather than compulsorily enjoy physical activities, and this will successfully result in a physically active lifestyle [22].

The Koshu Group Activity, Active Play and Exercise (GRAPE) study is a two-arm cluster randomised controlled trial (RCT) conducted in elementary schools and with wait-list control groups to examine the effects of active play programmes designed to address above-stated problems. The purpose of the Koshu GRAPE study is to clarify the effect of an active play programme that any child can voluntarily perform quickly and easily, without supervision, and to test the hypothesis that such programmes improve physical (PA and bone mass), mental (depressive symptoms), and social (non-cognitive skills, physical competence and school connectedness etc.) factors. This paper reports the rationale and study design of the GRAPE study. To the best of our knowledge, no studies have yet investigated the effect of programmes with very short durations (10 s per session, 1 min per day) of active play in elementary school children.

## 2. Materials and Methods

### 2.1. Study Design and Setting

The GRAPE study is a school-based two-arm (1:1) cluster randomised and wait-list controlled trial that was designed to improve PA and bone mass and reduce sedentary behaviour among children. It was conducted between December 2018 and December 2019 and targeted all 13 municipal public elementary schools in Koshu City, a rural area in the Yamanashi prefecture of Japan. Presently, there is an ongoing community-based prospective birth cohort study, namely Project Koshu, being conducted in the city since 1988. Under Project Koshu, all expectant mothers who responded to a survey during the obligatory visit to the city office for pregnancy registration were recruited, and their children were followed-up until graduation from junior high school [23].

### 2.2. School Recruitment

All elementary schools in Koshu City were invited to participate in the study (Figure 1). Eligible public elementary schools (n = 13) received a brief explanation regarding the GRAPE study during a conference wherein all the principals of Koshu City schools were gathered. At a later date, the principal and school nurse (yogo-kyoyu) at each school received a detailed presentation about the GRAPE intervention, the study’s evaluation methods, and requirements of involvement. Thereafter, the principal was asked to return a signed consent form at a later day if the school was interested in participating in the study.

### 2.3. Participant Recruitment

Following school recruitment, eligible children within each school were invited to participate in the study. Fourth and fifth grade (aged 9–11 years) boys and girls who did not have any medical conditions that prohibited their participation in active play programmes were eligible. This age group was selected because the children therein were capable of responding to questionnaires, could independently handle accelerometers with minimal assistance, and could be followed up for one year while being in elementary school. Potential participants were excluded if they were absent from school for long-term for reasons such as depression.

### 2.4. Interventions

#### 2.4.1. Active Play Programme

An active play programme was conducted in each elementary school for six months (from 15 January 2019 to 28 June 2019). The intervention required the children (≥2) to jump for approximately 10 s per session, at least five times a day (approximately 1 min/day). These short periods of activity were designed to be easy and enjoyable for everyone. Excluding the spring break, the intervention period lasted for 21 weeks. The participants performed three types of activities during the first week, with a new type of activity added each week to prevent the children from getting bored, providing a total of 24 activity types. Additionally, the activities were to involve any of the elements of the four categories of games distinguished by Caillois: Agon (competition), Alea (luck/chance), Mimicry (mimesis), and Ilinx (vertigo) [24]. To explain each activity, an instruction manual sheet (Figure 2), describing the method and illustration, was placed in each classroom. Moreover, a miniature version of the same instruction manual was distributed to each child by the homeroom teacher, and each child understood how to perform the activity themselves. However, since this programme aimed at encouraging children to play spontaneously, the classroom teacher was informed not to enforce an activity if the children had not implemented it. 

#### 2.4.2. Challenge Card

Additionally, a record card was used, which utilised human behavioural characteristics based on behavioural economics to encourage children to enjoy the activities continuously. Specifically, a challenge card that adopted a rank-up/down system that triggered esteem needs and loss aversion (a cognitive bias that refers to the human tendency to prefer avoiding losses to acquire equivalent gains) in addition to a visualisation of results was used (Figure 2). To confirm the rank, children attached their current rank sticker to the challenge card. If children achieved their rank-wise weekly goals, their ranks were increased the next week (rank order: seeds → growth → silver → gold → star (or heart) → diamond), and if they could not achieve their goals, their next week’s ranks were decreased. Children who conducted the activities together were instructed to record each other.

#### 2.4.3. Watching Videos

In order to maintain long-term awareness of active play in the GPAPE programme even after the completion of the intervention, participants of the intervention group watched an approximately 2-min-long movie with the message that physical activities such as standing, walking, playing with friends, etc., can be definite exercise even if it does not involve strenuous activities (https://youtu.be/dcr8aUpd3wk, accessed on 19 March 2021).

#### 2.4.4. Wait-List Control Group

During the intervention period, the participating school children belonging to the wait-list control group continued their routine school life and only underwent evaluation similar to the intervention group. After the final evaluation in December 2019, the wait-list control group received an activity programme similar to the intervention group but more selective and compact (intervention period: three months).

### 2.5. Outcome Measures

#### 2.5.1. Primary Outcome

The primary outcomes of the study were the objectively measured changes in PA level (moderate-to-vigorous PA, MVPA) from baseline to one-year follow-up (six-month post-intervention follow-up) and post-intervention changes in bone mass indicated, measured using quantitative ultrasound parameters (e.g., Stiffness index calculated from speed of sound (SOS) and broadband ultrasound attenuation (BUA).

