### 2.6. Data Collection

Objectively measured PA and questionnaire data were collected at four time-points: at baseline; a four-week follow-up (mid-intervention); a 6-month follow-up (immediately post-intervention); and a one-year follow-up (six-month post-intervention). Bone mass data were collected at two time-points: during September 2018 as a baseline measure and during September 2019 as a follow-up measure; both collections coincided with the health check-up routinely conducted at the beginning of the second semester (Table 1).

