### 2.8. Randomisation

Randomisation was conducted at the school level after baseline data were collected. This study was conducted in nine schools (18 classes, one class in each 4th and 5th grade; Figure 1). These schools were matched by size (total number of children) and region (Enzan or Katsunuma area) into four pairs. These pairs and one school with the smallest number of children in Koshu City were randomly assigned to either the intervention group or the control group using random numbers in Microsoft Excel by a researcher who was not directly involved in the implementation. The schools were each assigned a random number, and the school with odd last digits random number in each pair was assigned to the GRAPE intervention group. If the last digit was the same, GRAPE intervention group was assigned by the last second digits random number.

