### 2.10. Statistical Analysis

For inter-group comparisons of characteristics at baseline, independent t-tests and chi-square tests will be used for continuous and categorical variables, respectively. Missing values will be complemented using the multiple imputation method, which is integrated using Rubin’s formula [42], by creating 20 datasets under the assumption of the missing measurement mechanism of missing at random (intention-to-treat). To evaluate the effect of the intervention programme, a general linear mixed model will be employed for the analysis of continuous variables. Sensitivity analysis will be conducted for complete case analysis excluding data with missing values. Regarding the analysis of dichotomous secondary outcomes, the intervention effect will be examined by comparing the odds ratio estimated using multi-level (logistic model) regression analysis. Additionally, subgroup analysis will be performed in the population disliking exercise or precontemplation stage of transtheoretical model of behaviour change. All statistical analyses will be performed using Stata SE version 15.1 (StataCorp, Spring, TX, USA).

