## 3. Discussion

This GRAPE study programme is the first study to examine whether voluntary and a very short active play program contributes to increased bone mass and PA in school-aged children. The study is expected to improve the participant’s health indicators, such as increased physical activity and bone mass, mental and social health, and non-cognitive skills, based on the hypothesis that even a small amount of time spent on active play involving jumping will show positive effects on daily repetition. Additionally, the results of this study will help to develop evidence-based effective exercise programmes and health education in schools wherein the effects relative to that in a control group were insufficiently explored. Moreover, by objectively evaluating physical activity using a consumer model wrist-worn accelerometer, it will be possible to validate results, and children will become aware of their own levels of physical activity. However, the interpretation of GRAPE study results will likely be limited owing to the lack of generalizability as the participants were selected from a single rural area. The clusters were small, and there were not enough participants within the clusters, which resulted in a bias between the intervention and control groups. Moreover, as many measures were self-reported by the children, it is possible that measurement errors will occur. Furthermore, because many outcomes will be evaluated, the problem of “multiple comparisons” will need proper attention.

The implementation of this RCT program was possible by building long-term relationships of trust and cooperation between the health promotion section of the city office, the board of education, each school, and researchers through the Koshu project for. Therefore, the findings of this study will be directly returned to the children, guardians, schools and local residents by reporting to the School Health Committee and creating posters or booklets. Thus, this study not only provides novel academic findings but also returns familiar and evidence-based information to the community; therefore, it will be an academically and practically meaningful study.

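### Both primary outcomes are defined as changes and the stated mixed model names no baseline adjustment; prespecifying each child's own baseline value as a covariate would be a free improvement

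*Protocol article*

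**What the plan says.** Section 2.5.1 defines the first primary outcome: "The primary outcomes of the study were the objectively measured changes in PA level (moderate-to-vigorous PA, MVPA) from baseline to one-year follow-up". The second is "post-intervention changes in bone mass indicated, measured using quantitative ultrasound parameters". The Abstract also describes both as changes.

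Baselines exist for both. Bone mass was measured "during September 2018 as a baseline measure and during September 2019 as a follow-up measure". MVPA was measured at four time-points, the first in December 2018 (Section 2.6 and Table 1). Section 2.8 places randomisation after baseline data collection, and Section 2.4.1 starts the programme on 15 January 2019.

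Section 2.10 gives the effect model in one clause: "a general linear mixed model will be employed for the analysis of continuous variables". It does not say whether the response is the change or the follow-up value, and it names no covariate. The one use of baseline data that it does state is descriptive: "For inter-group comparisons of characteristics at baseline, independent t-tests and chi-square tests will be used".

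Section 2.8 reports nine schools and says: "These schools were matched by size (total number of children) and region (Enzan or Katsunuma area) into four pairs"; the ninth school was randomised on its own. The Discussion adds that the clusters were small, "which resulted in a bias between the intervention and control groups".

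**The concern.** If the text is applied as it stands, the treatment effect is a difference in mean change with no baseline term. That choice has two weaknesses. First, a change score gives the baseline a fixed coefficient of 1, whereas the best linear predictor gives it about r. The excess weight adds noise. Second, if the arms differ by chance at baseline, subtraction over-corrects: the arm that starts higher tends to show a smaller change through regression to the mean.

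With only nine schools, a chance baseline difference is likely to be non-trivial, and precision is scarce. The variable that deals with both weaknesses is already collected.

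**Working it through.** **The plan's own figures first.** Section 2.7 uses d = 0.50 (5 SI with SD 10; 10 min/day with SD 20), alpha 0.05 (taken as two-sided) and power 0.80.

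- Per group: 2 × (1.96 + 0.842)² / 0.50² = 62.8, so 63.
- Design effect: 1 + (20 - 1) × 0.05 = 1.95.
- Total: 2 × 63 × 1.95 = 245.7, so 246.
- Recruitment: 245.7 / (0.7 × 0.9 × 0.9) = 433.3, reported as 433.

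All three figures reproduce. They do not depend on how baseline is handled, because Section 2.7 does not say whether the SDs are those of single measurements or of changes.

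**Child-level precision.** Take equal variance SD² at baseline and follow-up, with correlation r.

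- Change score: 2(1 - r) SD².
- Baseline-adjusted: (1 - r²) SD².
- Ratio of adjusted to change: (1 - r²) / [2(1 - r)] = (1 + r)/2.
- Difference: [2(1 - r) - (1 - r²)] SD² = (1 - r)² SD², which is never negative.

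**Shift from a chance imbalance.** A baseline difference D between the arms moves an unadjusted change contrast by (1 - r) × D, against the arm that starts higher. As an illustration only, take D = 0.25 SD, with the SDs read as those of a single measurement: 2.5 SI or 5 min/day.

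| r (assumed) | Change, × SD² | Adjusted, × SD² | Ratio | Shift, SI | Shift, min/day |
|---|---|---|---|---|---|
| 0.3 | 1.40 | 0.91 | 0.65 | 1.75 | 3.5 |
| 0.5 | 1.00 | 0.75 | 0.75 | 1.25 | 2.5 |
| 0.7 | 0.60 | 0.51 | 0.85 | 0.75 | 1.5 |
| 0.9 | 0.20 | 0.19 | 0.95 | 0.25 | 0.5 |

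Against the planned 5 SI or 10 min/day, the shift is 35%, 25%, 15% and 5%.

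**Is such an imbalance plausible?** Use the plan's ICC of 0.05 and 20 children per school. Assume a 4 versus 5 split of schools and ignore any benefit of matching.

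- Variance of a school mean: 0.05 + 0.95/20 = 0.0975 SD².
- Standard error of a chance baseline difference: √[0.0975 × (1/4 + 1/5)] = 0.21 SD.

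The illustrative 0.25 SD is therefore only a little above one standard error.

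**Limit of the precision result.** Of the 0.0975, the between-school part is 0.05, or 51%. The ratio (1 + r)/2 governs the child-level part only. What adjustment does to the other half depends on the correlation between baseline and follow-up school means, which the article does not give.

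**Equivalence of the two responses.** If change = a + b·arm + c·baseline, then follow-up = a + b·arm + (c + 1)·baseline. The arm coefficient b is the same, so the definition in 2.5.1 can stay.

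**The case against.** The strongest objection is that the lack of adjustment is read from silence. This is a condensed article, and the covariate list of a mixed model often sits in a fuller document. Defining an outcome as a change does not fix its analysis: the change can be regressed on arm and baseline, or, for MVPA, baseline can enter a repeated-measures model as one of the four time-points. Over repeated randomisations an unadjusted change contrast is also unbiased.

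Much of this stands and limits what can be said. A reader might infer that the plan rules out baseline adjustment, or uses the baselines for subtraction and nothing else; no sentence says so. A reader might take the Discussion to concede that MVPA or SI differed at baseline. It speaks of an unspecified bias, names no variable and gives no baseline values. A reader might also carry the child-level ratio over to the treatment effect, which the between-school share above does not allow.

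The objection does not remove the point. The change definition is stated, not inferred. Section 2.10 carries the only description of the primary effect model, and it is specific on other matters: 20 imputed datasets, Rubin's formula, a complete-case sensitivity analysis and the software version. A better analysis is available from data already collected, whatever value r takes below 1.

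**Conclusion.** The point holds as a free improvement and not as an error that invalidates the design. As written, the outcome definition and the model together give a change contrast with no stated baseline adjustment. Adding the child's own baseline lowers child-level variance by 35% at r = 0.3, 25% at 0.5, 15% at 0.7 and 5% at 0.9. It also removes a shift of (1 - r) times any chance baseline difference.

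These sizes rest on equal variances at the two times, an assumed r and, for the shift, one baseline slope within and between schools. The direction at child level does not depend on r. No overall percentage gain for the treatment effect is claimed, and none can be derived from the article. Nor does the article show that either primary outcome was in fact imbalanced at baseline.

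**What to change.** In Section 2.10, prespecify the primary analysis of each outcome as a linear mixed model for the follow-up value (or, equivalently, the change), with arm and the child's own baseline value of the same outcome as fixed effects and school as a random effect. The baselines are the December 2018 MVPA and the September 2018 SI.

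Do not make region, school size or pair terms a requirement. Nine schools in two arms leave 9 - 2 = 7 degrees of freedom between schools. Region and size would leave 5; indicators for four pairs plus the single school would leave 7 - 4 = 3. The child-level baseline does not draw on these in the same way.

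The cost is one sentence. Section 2.5.1, the data collection and the sample size need no change.
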